- a Screening for Covid-19 as part of a screening study (cross-sectional survey, source population). Screening and Day 1 evaluations may occur on the same day if the point of care antigen SARS-CoV-2 tests result is positive. This depends on the malaria status of the patient (i.e. malaria positive: Invite eligible participants to enrol in the nested malaria treatment trial on Day-0; malaria-negative: Provide the participant with the option to enrol in the COVID-19 cohort study either the same day (Day-0) or wait until the confirmatory PCR results are available on Day-1 (see e, below)). A sub-group of participants who test negative by both SARS-CoV-2 antigen RDT and malaria RDT, and are feeling well, will be invited to participate as healthy controls.
- b These evaluations will be conducted by telephone and/or text messaging
- c These evaluations will be conducted among participant enrolled in the nested malaria treatment trial only
- d Any default diagnostic swab performed by local health authorities is acceptable. Additional swabs will be taken for a SARS-CoV-2 point of care antigen test.
- e The number of days for the SARS-CoV-2 test results to become available can be longer than 1 day and may vary by site.
- f Blood sample for SARS-CoV-2, malaria diagnostics and malaria and non-malaria serology in source population (fingerpick, 250 µL dried blood spot and malaria RDT). Consenting healthy control participants will provide a single 5 mL venous blood sample for CyTOF for B and T cell markers (fixed whole blood), Olink immunoassay (plasma) and transcriptional profiling (gene expression).
- g Saliva sample (~1mL) for SARS-CoV-2 RNA and antigen detection and SARS-CoV-2 and malaria serology
- h Includes questions for the WHO Ordinal Scale for Clinical Improvement and/or modified Flu-PRO PLUS
- i Daily during the first 14 days, or until the participant is asymptomatic for two consecutive days, whichever comes last, and then on days 21, 28 and 42
- j Mid-nasal swabs for research specific molecular detection and viral load and sequencing of SARS-CoV-2 (for later batch analysis, not for patient care)

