- k Blood sample (15mL on day-1 & 28, month 3, 6, and 12; 10mL on days 3, 7, 14, 21, 42) for anti-SARS-CoV-2 antibody titre (serum), cytokine/chemokine, inflammation and disease severity biomarker panel (serum), CyTOF for B and T cell markers (fixed whole blood), transcriptomics (gene expression), malaria and non-malaria serology (serum), malaria microscopy, malaria and non-malarial pathogen detection by molecular (e.g. PCR & TaqMAN, RDT), and (in malaria positive participants) genotyping to differentiate between recrudescence or reinfection (whole blood), biochemistry (day-1 and day-28 only), full blood count for haematology (day-1 & 28 only, or when clinically indicated), host genetics (blood pellet/dried blood spots) and QuantiFERON-TB Gold In-Tube (whole blood, at enrolment or otherwise at any other timepoint after enrolment if the QuantiFERON was missed at enrolment; a repeat QuantiFERON sample will be taken at 12m for all). In children, the total volume of blood will be 2.5mL in children weighing <10kg and 5mL in children weighing 10-<15kg.
- l Blood sample for serology and for malaria microscopy and RDT. The day-21 & 42 visits are in the nested malaria treatment trial only.
- m Stool sample for detection of helminth infection, SARS-CoV-2 detection and culture.
- n Informed Consent procedures, randomization and initiation of malaria treatment may also occur on day 0 if participants test positive for malaria during the cross-sectional screening for SARS-CoV-2 by routine staff and by a SARS-CoV-2 antigen test (see d, g, above). If the SARS-CoV-2 test results turn out to be negative, the patient will complete the 3-day treatment course as assigned but will be considered a screening failure and not followed-up any further.
- o Study drug: ## denotes either artemether-lumefantrine (AL) twice daily, or pyronaridine-artesunate (PA) once daily (depending on group assignment). The first dose will be administered in the study clinic as directly observed therapy. All subsequent doses will be taken at home by the study participant if they are asked to self-isolate for home-based care, or by study/hospital staff for participants admitted to isolation wards.

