| 
 
To determine if malaria infection affects COVID-19 disease presentation and duration
 
                                                  | 
 
Symptoms and duration of COVID-19 by day-28 in cases with and without malaria
 
                                                                                                                                                                                                                                                                                           |
| 
 
To determine if malaria infection in COVID-19 patients alters the antibody response to SARS-CoV-2 infection
 
                           | 
 
Cumulative seroconversion rates* (total antibody, IgG, IgM, IgA) by days 7, 14, 21, 28, and total antibody, IgG, IgM, IgA antibody titres against SARS-CoV-2 by day-28 expressed as the geometric mean, maximum, and change from baseline
 
Seroreversion rates for IgG, IgM, IgA and geometric mean antibody titres against SARS-CoV-2 by month 3, 6 and 12
 
     |
| 
 
To determine if malaria infection in COVID-19 alters the inflammatory, genomic, and cellular immune responses to SARS-CoV-2 infection
 
 | 
 
Multiplex serum cytokine markers; Transcriptional profiling (gene expression) of whole blood; Fixed whole blood for T and B cell markers by day-28
 
                                                                                                                                                                                                                      |
| 
 
To determine if malaria infection in COVID-19 alters the viral load or duration of SARS-CoV-2 infection
 
                               | 
 
Median viral load of SARS-CoV-2 detected from mid-nasal swabs by PCR
 
Cumulative incidence of SARS-CoV-2 clearance (defined as the proportion of participants with negative nasal swabs) by days 7, 14, 21 and 28
 
Time to clearance of nasal SARS-CoV-2, defined as negative SARS-CoV-2 RNA PCR tests (swabs collected on days 1, 3, 7, 14, 21 and 28)
 
 |

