### 5.1.2 COVID-19 cohort study (N~708)

All SARS-CoV-2 positive participant from the source population will be eligible for enrolment in the COVID-19 cohort study of *confirmed* COVID-19 cases regardless of their malaria status. The COVID-19 cohort study has a clinical disease progression component and an immunological component. It also has a nested malaria treatment trial in a subgroup of participants that are co-infected with malaria (see 5.1.3, Nested malaria treatment trial within the COVID-19 cohort study, below). The primary aim is to determine if symptomatic or asymptomatic malaria infection affects the clinical course of COVID-19. Some elements of the immunological component involve all participants in the COVID-19 cohort study (e.g. antibody responses), and some involve a subset of approximately 180 participants (e.g. cellular responses) from whom more detailed immunologic profiling of serial samples of serum and whole blood will be analysed and compared between participants with and without malaria. All cohort participants will be followed on days 0, 3, 7, 14, and 28 to monitor disease progression, cumulative seroconversion rates, viral load, and viral carriage. Additional samples will be taken at 3, 6, and 12 months to determine the duration of the protective antibody responses to the SARS-CoV-2 virus.

All COVID-19 patients without malaria will be treated with the recommended standard of care (SOC) at the time of enrolment. The SOC will follow the national guidelines in each country and are subject to change (see 7.1.1, Interventions, COVID-19 cohort study, page 33). All COVID-19 patients with malaria will be enrolled in the nested malaria treatment trial and have additional samples taken at day 21 and day 42, as described in section 5.1.3, below.

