### 5.1.3 Nested malaria treatment trial within the COVID-19 cohort study (N~142)

In addition, we will conduct a nested exploratory, 6-week, open-label, 2-arm, randomised controlled nested malaria treatment trial in the COVID-19 patients co-infected with malaria with mild disease who are able to take oral medication. We will compare pyronaridine-artesunate and artemether-lumefantrine to assess whether, in COVID-19 patients with malaria, treatment with quinoline antimalarials (pyronaridine) affects the seroconversion rate or time to seroconversion to SARS-CoV-2 or reduce viral load and duration of shedding relative compared to patients receiving AL. The patients enrolled in this nested malaria treatment trial will have an additional follow-up visit at days 21 and 42.

The follow-up schedule in the treatment study will be identical to that in COVID-19 patients without malaria to allow for comparison between disease progression between COVID-19 with and without malaria.

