### 9.1.1 Pre-screening with point of contact (POC) SARS-CoV-2 antigen tests

The screening study (cross-sectional survey, source population) includes pre-screening with an experimental POC SARS-CoV-2 antigen tests and Government approved antigen tests. At the time of writing (September 2020), there are no approved SARS-CoV-2 antigen tests yet in Kenya or Burkina, but this may change during the course of the study. We will follow the national guidelines in each country. In Kenya GeneXpert, antigen-RDT and PCR results are considered for definitive diagnosis of COVID-19. If a participant tests COVID positive for any rapid antigen tests, GeneXpert, or PCR, the participant shall be enrolled.

Eligible patients with both a positive SARS-CoV-2 test and a positive malaria test on Day-0 require malaria treatment that same day and will be invited to enrol in the COVID-19 cohort study and the nested malaria treatment trial on Day-0; i.e. prior to knowing the SARS-CoV-2 PCR results (see 9.2.1.3, Nested malaria treatment trial, page 43). Patients with a positive antigen test but negative for malaria will be invited to participate in the COVID-19 cohort study and can choose whether to enrol that same day (Day-0) or wait until the confirmatory PCR results become available (typically on Day-1).

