### 9.2.2 *Scheduled follow-up visits day 3, 7, 14, 21, 28 and 42*

We will follow local MoH guidelines in each country to determine if a participant requires hospitalisation and for how long, or if a participant will be invited to self-isolate at home.

Participants who are self-isolating will be asked to return to the study clinics for scheduled follow-up visits on days 3, 7, 14, 21, 28 and 42. Of these visits, the follow-up visits on day 21 and 42 apply to the participants enrolled in the nested malaria treatment trial only. During each of these scheduled follow-up visits, a similar symptom questionnaire will be filled out, concomitant medication will be reviewed, and brief physical examination performed, and the respiratory rate and pulse, body temperature and O2 saturation taken by study staff. The participant will be asked to bring the form with the self-assessed values for body temperature and O2 saturation values that were taken by the participant at home for verification of the data and the technique used by the participant. A photo will be taken of the self-assessment form for subsequent data entry and verification. Where relevant, any relevant demographic or health-related information will again be copied from existing hospital and clinic records. Similar venous blood samples (ml), swab samples will be taken as on enrolment.

Participants who will be admitted on isolation wards will be monitored daily for signs and symptoms of severe COVID-19, and have daily respiratory rate, body temperature and O2 saturation measured. Similar blood and swab samples will be taken for participants who are self-isolating.

If participants are enrolled in the nested malaria treatment trial will have an additional 5mL of whole blood taken for antimalarial drug levels from the same blood draw as the overall sample (i.e. the total blood volume per blood draw on days 3, 7, 14, 21, 28 and 42 will be 20mL (15mL for the above-mentioned assays under 'k' in the section 2.2.4, Schedule of activities page 19 and 5mL for pharmacokinetics). The volume samples in children below the age of assent will be less and based on bodyweight (total 2.5 mL <10kg and 5 mL 10-<15kg per sample) (see section 12.7.1.4, Maximum blood volume, page 63) and will be excluded from the pharmacokinetic sampling.

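### Cohort endpoints compare malaria-positive with malaria-negative participants at day 21, but only nested-trial participants, all malaria-positive, are sampled that day

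*Protocol*

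**What the plan says.** **Who is sampled on day 21.** Four places in the protocol agree:

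- Section 9.2.2: "the follow-up visits on day 21 and 42 apply to the participants enrolled in the nested malaria treatment trial only".
- Section 2.2.4, footnote c, attached to the day-21 swab and blood cells: "These evaluations will be conducted among participant enrolled in the nested malaria treatment trial only".
- Section 2.2.4, footnote l: "The day-21 & 42 visits are in the nested malaria treatment trial only".
- Section 5.1.2: "All cohort participants will be followed on days 0, 3, 7, 14, and 28 to monitor disease progression". Day 21 is not in that list. The same section describes the day-21 and day-42 samples as additional ones for patients with malaria.

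**What the cohort endpoints require.** Section 4.2, repeated in the registration data in 2.2.3, lists these for cases with versus without malaria:

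- For viral clearance: "Cumulative incidence of SARS-CoV-2 clearance (defined as the proportion of participants with negative nasal swabs) by days 7, 14, 21 and 28".
- For antibodies, cumulative seroconversion by the same four days. It is defined as a positive antibody test in the period among those negative at enrolment.
- For the duration of shedding, an endpoint whose swab list includes day 21: "Time to clearance of nasal SARS-CoV-2, defined as negative SARS-CoV-2 RNA PCR tests (swabs collected on days 1, 3, 7, 14, 21 and 28".

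**What conflicts with the four places above.**

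- Section 5.1.3: "The follow-up schedule in the treatment study will be identical to that in COVID-19 patients without malaria".
- The lay summary (2.2.1) has all 708 patients seen on days 21 and 42. The abstract (2.2.2) lists those days without restriction.
- Table 2 in 12.7.1.4 counts day-21 and day-42 draws in its cohort row.
- Section 10.4.2 lists the serology days without day 21, whereas footnote k of the schedule includes a day-21 draw for antibody titres.

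**The concern.** The extra sample goes with the exposure being compared. A malaria-positive participant in the nested trial who clears virus between days 14 and 21 can be recorded as clear on day 21. A malaria-negative participant with the same course cannot be recorded as clear before day 28. Looking more often in one group makes that group appear to clear and seroconvert sooner. The bias always runs in the same direction, and a larger sample does not reduce it.

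These endpoints bear on the first two null hypotheses in section 3.3, on viral shedding and on the immune response. An artefact could be read as malaria, or its treatment, speeding up clearance.

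**Working it through.** **1. The plan's own figure.** Section 11.1.1 gives 30% versus 45%, malaria-positive to malaria-negative 1:4, alpha 0.05 (two-sided, 11.2.1) and 5% loss. With the pooled-variance formula, r = 0.25 and p̄ = (0.30 + 0.25×0.45)/1.25 = 0.33:

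n(negative) = [z(α/2)·√((1+1/r)·p̄·(1−p̄)) + z(β)·√(0.30×0.70 + 0.45×0.55/r)]² / 0.15²

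- 90% power: [1.960×1.0514 + 1.2816×1.0954]²/0.0225 = 534. Then 534×1.25 = 667.5, so 668 completers, and 668/0.95 gives 704 enrolled (stated: 673 and 708). Power at the stated 135 and 538 completers is 90.3%.
- 80% power: 396×1.25 = 495, and 495/0.95 gives 522 (stated: 522).

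The plan's figures reproduce closely, so 135 and 538 are used below.

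**2. Can visit windows fill the gap?** Day 14 is ±3, so it closes on day 17. Day 28 opens at −3, which is day 25, in both versions of the schedule header. Day 21 is ±3, covering days 18 to 24. A malaria-negative participant has no scheduled swab in that span.

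**3. Clearance by day 21 with no malaria effect.** The only clearance rate in the protocol is 20% by day 7 (section 11.1.3, the artemether-lumefantrine planning value). Assume a constant hazard, the same in both groups, and count an unscheduled swab as not yet clear:

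- Malaria-positive, last look day 21: 1 − 0.8³ = 48.8%.
- Malaria-negative, last look day 14: 1 − 0.8² = 36.0%.
- Risk ratio 0.488/0.360 = 1.36; difference 12.8 points.

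**4. Chance of p<0.05.**

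- Pooled proportion (135×0.488 + 538×0.360)/673 = 0.386.
- Null SE √(0.386×0.614×(1/135 + 1/538)) = 0.0469.
- Alternative SE √(0.488×0.512/135 + 0.360×0.640/538) = 0.0477.
- (0.128 − 1.96×0.0469)/0.0477 ≈ 0.76, so about 78%.

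**5. Sensitivity to the curve.** Take a Weibull curve with shape k, which is an assumption. Calibrated to 20% by day 7, clearance by days 14 and 21 is 1 − 0.8^(2^k) and 1 − 0.8^(3^k). Seroconversion uses the planning value of 50% by day 14 (11.1.3), so day 21 is 1 − 0.5^(1.5^k).

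| k | Clearance by day 21, positive vs negative | RR | P(p<0.05) | Seroconversion by day 21, positive vs negative | RR |
|---|---|---|---|---|---|
| 1 | 48.8% vs 36.0% | 1.36 | 78% | 64.6% vs 50.0% | 1.29 |
| 1.5 | 68.6% vs 46.8% | 1.47 | >99% | 72.0% vs 50.0% | 1.44 |
| 2 | 86.6% vs 59.0% | 1.47 | >99% | 79.0% vs 50.0% | 1.58 |

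No rejection rate is given for seroconversion, because its denominator is limited to those seronegative at enrolment and the protocol does not give that number.

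**6. Time to clearance.** In 2,000 simulated cohorts of 135 versus 538, clearance was dated at the first negative swab and compared by log-rank test. The same curve was used in both groups, calibrated to 20% by day 7.

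| k | Mean recorded days, positive vs negative | Rejection, unequal visits |
|---|---|---|
| 1 | 20.3 vs 21.2 | 11% |
| 1.5 | 18.3 vs 19.8 | 57% |
| 2 | 16.3 vs 18.2 | 98% |

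With the same visits in both groups, rejection was 4 to 6%.

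**7. Day 28.** Both groups are swabbed, so the proportions agree if clearance is permanent. Suppose each swab from a still-positive patient reads negative with probability 5%, 10% or 20%, and any negative counts. The extra look then adds 1.7, 2.7 or 3.4 points in malaria-positive participants (constant hazard).

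**The case against.** **The 78% rests on a rule the protocol does not state.** Nothing says that an absent day-21 swab counts as not cleared. The one missing-outcome rule, in 11.2.6.2, is complete case without imputation, given for the primary analysis. This stands, and the figure must be labelled conditional. It does not rescue the endpoint: under complete case the malaria-negative group has no day-21 value at all.

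**The log-rank test is not in the plan.** Section 11.2.4 names no time-to-event method, and 11.2.1 defers detail to a SAP that was not available here. The missing method is therefore not a fault in itself, and an interval-censored analysis would remove the bias. No SAP, however, can supply swabs that were never taken. The by-day-21 proportions need a change to the endpoint or to the schedule.

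**Serology may not be affected in this way.** If section 10.4.2 governs, neither group has a day-21 antibody result, and the problem becomes an endpoint without data. This stands until the text is reconciled.

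**'Identical' may be loose wording.** The sentence before it in 5.1.3 mentions the extra visits, and the stated purpose is to compare disease progression. That is fair, but read literally the sentence is untrue.

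**A reader might also infer that the clock differs between groups**, with malaria-positive participants entering on day 0 and malaria-negative ones later. The documents do not support this. Malaria-negative participants with a positive antigen test "can choose whether to enrol that same day (Day-0) or wait until the confirmatory PCR results become available (typically on Day-1", so day-0 entry is open to them. For malaria-positive participants, footnote n of the schedule permits day-0 enrolment without requiring it, and section 9.2.1.3 allows malaria testing on day 1. The 72-hour limit on test results, extendable to 120 hours, applies to both groups. No systematic lag can be derived.

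**Conclusion.** Wrong as written, and it should be fixed, but it affects secondary cohort endpoints only. Section 4.2 asks for a between-group comparison at a visit that one group does not have. The by-day-21 endpoints are therefore either biased towards earlier clearance and seroconversion in malaria-positive participants, or cannot be estimated.

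The size of the bias (risk ratio 1.36, about 78% chance of a spurious p<0.05) depends on three assumptions: an unscheduled visit counts as not yet, the nested trial's control-arm planning rate applies to the whole cohort, and the hazard is constant. Steeper curves give a larger ratio. For time to clearance the direction is firm if events are dated at visits. The size is not: it runs from 11% to 98% rejection across the shapes tried, and depends on the analysis method.

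Malaria-positive participants who are ineligible for the nested trial also lack day 21, which dilutes the effect slightly.

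It would be too strong to infer that the main results are compromised. The cohort primary endpoint (progression by day 28) is unaffected. So are the day-7 and day-14 comparisons and the randomised pyronaridine-artesunate versus artemether-lumefantrine comparison, where both arms share one schedule.

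**What to change.** - In 4.2 and 2.2.3, delete day 21 from the cohort clearance and seroconversion endpoints and from the cohort time-to-clearance swab list. Keep it for the pyronaridine-artesunate versus artemether-lumefantrine comparison.
- State in section 11.2 that every malaria-positive versus malaria-negative comparison of swab or blood results uses only the common visits (days 1, 3, 7, 14, 28). For time to clearance, an interval-censored analysis that uses each participant's actual swab dates is an acceptable alternative.
- Reconcile 2.2.1, 2.2.2, 5.1.3 and Table 2 in 12.7.1.4 with 2.2.4, 5.1.2 and 9.2.2.
- Reconcile 10.4.2 with footnote k on whether day-21 serology is done at all.

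The cost is wording. The cohort comparison gives up a time point that the malaria-negative group never had, and the randomised comparison loses nothing. Sampling malaria-negative participants on day 21 as well, as the summaries imply, would also remove the asymmetry, but at about 566 further visits and only for people not yet past that day.

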- p Pharmacokinetic samples: Blood (5mL) and saliva (0.5mL) sample for pyronaridine concentrations. The pharmacokinetic blood sample will be taken from the same blood draw as under 'k' above, but the total volume increased to 20mL (15mL for the above-mentioned assays under 'k' and another 5mL for pharmacokinetics) on Day-1 and Day-28, and 15mL (10mL + 5mL) on days 3, 7, 14, 21, and 42. Of the 5mL for the pharmacokinetics, 2.5mL will be stored as whole blood, and the remaining 2.5mL will be processed and stored as plasma. Children under the age of assent (<12 years in Burkina Faso and <13 years in Kenya) will be excluded from pharmacokinetic sampling.

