### 12.7.1.4 Maximum blood volume

In adults and older children above the minimum age of assent, a blood sample of no more than 20mL per sample will be taken at days 1 (enrolment) and day-28 (close-out) and 15mL on each of the five scheduled visits up to day 42 inclusive (day 3, 7, 14, 21 and 42) and during the extended follow at 3, 6, and 12 months. Thus the total cumulative volume of blood collected from each participant will be small (130.25mL in the first three months [0.25 mL at screening, 2 further blood draws of 20mL and 5 blood draws of 15mL in the first 42 days plus one 15mL blood draw at three months] and 160.25 mL in total over 12 months [two additional 15mL blood draws at 6 and 12 months] and well within the accepted limit of 500mL over three months as stipulated by the KEMRI–Wellcome Trust Research Programme, Kilifi, Kenya guidelines for the maximum volume per participant and other international guidelines. Where possible routine care and study-specific samples will be combined in a single blood draw.

Table 2 Maximum blood volumes in children per bodyweight category

|                                                          | 5.5 b –
<10 kg | 10 –
<15 kg | >=15kg –
<12/13 yrs | >=12/13 years
(~>=27.7kg) a |
|----------------------------------------------------------|------------------------------|----------------|------------------------|-------------------------------------------|
| Weight in Kg in weight category                          | <10 kg                       | <15 kg         | <12/13 yrs             |                                           |
| Maximum weight in Kg in weight category                  | <10                          | <15            | <22.2                  |                                           |
| Screening study volume (mL)                              | 0.25                         | 0.25           | 0.25                   | 0.25
(2x20) + (5x15)                   |
| Cohort study Days 1, 3, 7, 14, 21, 28, 42 (mL)           | 7x2.5=17.5                   | 7x5=35         | 7x7.5=52.5             | = 115                                     |
| 3 month follow-up visit (mL)                             | 2.5                          | 5              | 5                      | 15                                        |

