Younger children below the age of assent (Burkina Faso 12 years, Kenya 13 years) will be excluded from the pharmacokinetic sampling to minimize the blood volume in younger children as the pharmacokinetic sample requires 5mL. Children below 10kg bodyweight will have 2.5mL instead of 20mL or 15mL blood draws taken during follow-up in addition to the finger/heel prick on Day-0 (250 uL) (a cumulative total of 20.25mL by over three months and 25.25 mL over 12 months). This ensures that even the lightest six months old children (the minimum age at enrolment) remain below the safety limit of 5mL/kg over three months (corresponding to a bodyweight of 4.1 kg for eight blood draws of 2.5 mL per sample) because the first percentile at the age of six months of the WHO weight-for-age reference is 5.5kg in girls. Similarly, the volume for children weighing 10- <15kg will be 5mL per draw, and 7.5mL for children weighing 15kg or more until the age of assent. At the age of assent (12 years in Burkina Faso and 13 years in Kenya), they are eligible for the nested malaria treatment trial and 20mL (Days 1 and 28) or 15mL (days 3, 7, 14, 21, 42) per sample will be taken, or 120.25mL over three months and within the 3-month safety limit of 138.5mL (based on the 1st percentile for weight-for-age of 10 year old and an average weight gain of 25% in girls between 10 and 12 years of age.). The cumulative volume by 12 months will be 130.25mL (see Table 2, above).

Figure 5: Maximum blood volume per bodyweight in children for research in addition to blood taken for routine clinical care

[figure not shown]

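### Section 9.2.2 sets 20 mL at all six nested-trial follow-up draws, but the schedule footnotes and the blood-volume safety calculation use 15 mL on five of them, 25 mL less in total

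*Protocol*

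**What the plan says.** Section 9.2.2, which describes what happens at each follow-up visit, says of nested-trial participants that "the total blood volume per blood draw on days 3, 7, 14, 21, 28 and 42 will be 20mL". It breaks this down as 15 mL for the assays in footnote k of section 2.2.4 plus 5 mL for PK.

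The other places that give these volumes differ:

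- Section 2.2.4, footnote k (without PK): 15 mL on days 1 and 28 and at months 3, 6 and 12, but "10mL on days 3, 7, 14, 21, 42".
- Section 2.2.4, footnote p (with PK): 20 mL on days 1 and 28, and "15mL (10mL + 5mL) on days 3, 7, 14, 21, and 42".
- Section 12.7.1.4, opening text: at most 20 mL on days 1 and 28, and "15mL on each of the five scheduled visits up to day 42 inclusive (day 3, 7, 14, 21 and 42".
- Table 2, column for participants at or above the age of assent: two draws of 20 mL and five of 15 mL, 115 mL over days 1 to 42. The cumulative totals are 130.25 mL by three months and 160.25 mL by 12 months.
- Section 12.7.1.4, paragraph below Table 2: the same per-draw volumes up to day 42, but different totals, "or 120.25mL over three months and within the 3-month safety limit of 138.5mL" and "The cumulative volume by 12 months will be 130.25mL".

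On day 1, footnote p has "the total volume increased to 20mL (15mL for the above-mentioned assays under 'k' and another 5mL for pharmacokinetics) on Day-1 and Day-28". The PK row of the schedule has no mark on day 1, and section 10.6 lists PK samples on days 3, 7, 14, 21, 28 and 42 only.

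**The concern.** Section 9.2.2 cites footnote k for a 15 mL base volume that footnote k does not give on days 3, 7, 14, 21 and 42. The result is two different volumes for the same draw. The one in the visit instructions is the larger, and it is not the one that the safety calculation checked.

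The protocol sets itself a limit of 5 mL/kg over three months for repeated research draws in children. It justifies the volume at the age of assent (12 years in Burkina Faso, 13 in Kenya) at a reference weight of 27.7 kg. The margin there is small, so an extra 25 mL matters for the lightest minors.

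Two further slips belong to the same calculation. The totals in the paragraph below Table 2 do not agree with Table 2. And 5 mL of PK blood is counted on day 1 although no PK sample is scheduled that day.

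**Working it through.** **Inputs.** Screening fingerprick 0.25 mL (Table 2). Per-draw volumes as listed above. Month-3, 6 and 12 draws of 15 mL each (footnote k, Table 2). Limit 5 mL/kg and reference weight 27.7 kg (Table 2 and its footnotes).

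**The protocol's own figures reproduce.**

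- Limit: 27.7 × 5 = 138.5 mL.
- Days 1 to 42: 2 × 20 + 5 × 15 = 115 mL.
- By 3 months: 0.25 + 115 + 15 = 130.25 mL, which is 8.25 mL inside the limit.
- By 12 months: 130.25 + 2 × 15 = 160.25 mL.

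**The six follow-up draws.**

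- Section 9.2.2: 6 × 20 = 120 mL.
- Footnote p, 12.7.1.4 and Table 2: 5 × 15 + 20 = 95 mL.
- Difference: 25 mL, and 25/115 = 21.7% of the Table 2 volume for days 1 to 42.

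**Three-month total if 9.2.2 is followed.** Day 1 is 20 mL under footnote p, or 15 mL under the general cohort enrolment text in 9.2.1.2. The month-3 visit depends on funding (9.2.6), so both cases are shown.

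| Day 1 | Month-3 draw | Total (mL) | Against 138.5 mL |
|---|---|---|---|
| 20 mL | taken | 0.25 + 20 + 120 + 15 = 155.25 | 16.75 over (12.1%) |
| 15 mL | taken | 0.25 + 15 + 120 + 15 = 150.25 | 11.75 over (8.5%) |
| 20 mL | not taken | 0.25 + 20 + 120 = 140.25 | 1.75 over |
| 15 mL | not taken | 0.25 + 15 + 120 = 135.25 | 3.25 within |

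With the month-3 draw, the weight below which 5 mL/kg is passed is 155.25/5 = 31.05 kg or 150.25/5 = 30.05 kg.

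**Totals below Table 2.** They reproduce only with 5 mL at months 3, 6 and 12: 0.25 + 115 + 5 = 120.25 mL, and 120.25 + 2 × 5 = 130.25 mL. The amendment log records that these draws were raised from 5 to 15 mL, so the totals were evidently not updated. They are 10 mL too low at three months (130.25 − 120.25) and 30 mL too low at 12 months (160.25 − 130.25). The corrected three-month total is still within 138.5 mL.

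**If the day-1 PK volume is dropped.** Days 1 to 42: 15 + 20 + 5 × 15 = 110 mL. By 3 months: 0.25 + 110 + 15 = 125.25 mL. By 12 months: 125.25 + 30 = 155.25 mL.

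**The case against.** The practical risk is remote. Section 10.1 sends readers to the schedule in 2.2.4 for all samples, and footnote p there gives the right volume by day. Section 12.7.1.4 caps the five visits at 15 mL, and its main calculation is correct and within the limit. One sentence disagrees with several consistent statements, and no endpoint, analysis or sample size is touched.

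Passing the limit needs several conditions together: a minor at or above the age of assent, in the nested trial, sampled for PK, under about 30 to 31 kg, with staff working from 9.2.2 and nearly every draw taken. The 27.7 kg reference is the protocol's own 1st percentile, and 16.9.7 limits PK sampling to about 70 participants in the pyronaridine arm, although 9.2.2 words it for the whole nested trial. With day 1 at 15 mL, a minor at the reference weight passes the limit only if the month-3 draw is taken.

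On day 1, 12.7.1.4 sets a ceiling, and counting 20 mL in a table of maximum volumes is conservative.

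All of this stands, and it bears on how serious the point is. It does not remove the contradiction. The visit instruction misstates the footnote it cites and, followed as written, takes more blood than was checked. The totals below Table 2 do not derive from 9.2.2 and are a separate correction in the same section. The day-1 point is likewise separate: a ceiling is not contradicted by a smaller draw, but footnote p assigns 5 mL on that day to a sample that the schedule row and 10.6 do not contain.

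**Conclusion.** Section 9.2.2 is wrong as written. On days 3, 7, 14, 21 and 42 the intended volume with PK is 15 mL, and following 9.2.2 would add 25 mL per PK-sampled participant who gives all five draws.

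The main safety calculation is sound. For adults the excess has no bearing on the 500 mL limit, and children below the age of assent have no PK sampling and are unaffected. For the lightest minors at or above that age, the three-month total would be 150.25 to 155.25 mL with the month-3 draw, against 138.5 mL at 27.7 kg. This assumes that staff follow 9.2.2 and that every scheduled draw is taken. The number of such participants may be very small, and the documents do not allow it to be estimated.

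The point should be fixed. It is a limited error with a clear correction that lowers the volume instructed.

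**What to change.** 1. In 9.2.2, state 15 mL (10 + 5) on days 3, 7, 14, 21 and 42, and 20 mL (15 + 5) on day 28.
2. In the paragraph below Table 2 in 12.7.1.4, replace 120.25 and 130.25 mL with 130.25 and 160.25 mL.
3. Settle the day-1 PK volume in footnote p and 12.7.1.4 one way or the other:
   - Drop it. Day 1 becomes 15 mL, days 1 to 42 total 110 mL, and the cumulative totals in 12.7.1.4 and Table 2, including those in item 2, become 125.25 mL (3 months) and 155.25 mL (12 months).
   - Or add a day-1 PK sample to the schedule row and to 10.6, and keep 130.25 and 160.25 mL.

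The 15 mL in 9.2.1.2 is the general cohort volume, agrees with footnote k and can stay. If the day-1 sample is added, the nested-trial enrolment text in 9.2.1.3 is the natural place to mention the extra 5 mL.

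The cost is a text correction in one amendment. Table 2 changes only if the day-1 PK volume is dropped. Nothing in the design, sample size or analysis changes.
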